#### Exclusion criteria

Patients will be excluded from the trial if they:
Are diagnosed with central sleep apnea/hypopnea syndromeHave concurrent systemic diseasesHave rhinostenosisHave a z score equal to or greater than 3 based on the body mass index (BMI).

### Who will take informed consent? {26a}

A qualified clinical research assistant will obtain written informed consent from the guardians of participants after full explanation of this study.

### Additional consent provisions for collection and use of participant data and biological specimens {26b}

On the consent form, guardians will be asked if they agree to the use of their children’s data should they choose to withdraw from the trial. They will also be asked for permission for the research team to share relevant data with people from the universities taking part in the research or ethics committees or regulatory authorities, where relevant. This trial does not involve collecting biological specimens for storage.

## Interventions

### Explanation for the choice of comparators {6b}

Due to poor compliance, the application of CPAP for pediatric OSAHS is decreasing in the clinic. The most commonly used treatments are medication, AT, and orthodontic treatment. For children with mild OSAHS and mandibular retrognathia, both orthodontic treatment and AT may be effective in terms of PSG data and maxillofacial development, but there is no evidence-based medical research to compare the efficacy of AT and/or orthodontic treatment. Furthermore, we wondered what the indications are for the use of these two therapies, individually or in combination. Thus, in this study, the comparators included a drug treatment group, a surgical treatment group, an orthodontic treatment group, and a surgery and postoperative orthodontic group.

### Intervention description {11a}

All subjects will receive different treatments, i.e., drug treatment, surgical treatment, orthodontic treatment, and surgery or postoperative orthodontic treatment, within 4 weeks after randomization. The practitioners will be doctors who have a minimum of 5 years of work experience in their hospital and have undergone training in the trial protocol prior to the study. The training mainly includes information on the recruitment and randomization of subjects, the standardized treatment procedures, the completion of the case report form (CRF), and the adverse event reporting system.

Drug treatment group: Patients in this group will receive mometasone furoate aqueous nasal spray once a day (0.1 mg) in the morning for 2 months. The research assistants will interview the participants’ parents by telephone to remind the patients of the treatment stage.

Surgical treatment group: Patients in this group will receive AT under general anesthesia. Routine follow-up will be conducted 2 weeks after surgery to evaluate the surgical effects and the prognosis.

Orthodontic treatment group: Patients in this group will receive orthodontic treatments. They will receive orthodontic treatment according to a consistent comprehensive protocol, which mainly involves the use of a removable twin-block appliance combined with RME (see Fig. 2).

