### Criteria for discontinuing or modifying allocated interventions {11b}

Participants may quit the study at their guardians’ discretion or defer to the supervisory team. Circumstances that will suspend participants from the study include adverse events and detection of evidence that may influence the outcomes of the research. Subjects who leave the study will be followed up until they are in stable status.

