### Provisions for post-trial care {30}

Participants may quit the study at their guardians’ discretion or defer to the supervisory team if they are not responding well to treatment. They will be followed up and receive appropriate therapy free of charge after they leave the study.

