#### Primary endpoint

The primary endpoint of the trial is the mean change in AHI from baseline (M 0) to the primary endpoint (M 7), because PSG is still the gold criterion for diagnosing OSAHS. All subjects will undergo attended overnight PSG in a hospitalized ward. They will go to bed at their usual sleeping time and sleep for at least 6 h to ensure PSG monitoring time. A reduction in airflow of more than 90% compared to that preceding sleep breathing is considered to be an obstructive apnea. A hypopnea is defined as a reduction in airflow of more than 30%, accompanied with an oxygen desaturation of ≥ 3% and/or an arousal. A duration of the obstructive apnea or hypopnea equal to or greater than two respiratory cycles is defined as an obstructive event. The definition of AHI is the number of obstructive events per hour. The analysis will include mixed events but not central events.

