## Statistical methods

### Statistical methods for primary and secondary outcomes {20a}

Statistical analysis will be conducted using IBM SPSS Statistics (version 22.0). Descriptive analysis will be performed for all of our variates. The analysis set will consist of the intention-to-treat (ITT) set, per protocol (PP) set, and safety set. All subjects will be included in the ITT set after randomization regardless of whether they received the treatment or not. Subjects who complete treatment sessions (M 0 to M 7) without any major violation to the trial procedure will be included in the PP set. Participants who receive treatment will be included in the safety set for safety analysis. The significance level will be set so that *P* < 0.05 will be considered significant.

The primary endpoint of this study is the change in AHI from M 0 to M 7. Intergroup comparisons will be performed using an analysis of covariance (ANCOVA) to adjust for gender, obesity status, and baseline AHI. The outcomes will be mainly analyzed using the PP set. Linear regression will be used to evaluate the correlation between observed differences of AHI and the potential prognostic factors, such as gender, BMI, neck size, and research site.

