### Methods in analysis to handle protocol non-adherence and any statistical methods to handle missing data {20c}

Missing data will be dealt with using the last-observation-carried-forward (LOCF) method.

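### A child in any arm who leaves before M 7 for poor response is either dropped from the main per-protocol analysis or given an AHI change of exactly 0

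*Protocol article*

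**What the plan says.** Five statements in the protocol article act together.

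- **Endpoint and schedule.** The primary endpoint is the change in AHI from M 0 to M 7 (Primary endpoint). Table 1 and Outcomes {12} place polysomnography at M 0, M 7, M 12 and M 24 only.
- **Exit.** Provisions for post-trial care {30} lets participants quit, or "defer to the supervisory team if they are not responding well to treatment". It adds: "They will be followed up and receive appropriate therapy free of charge after they leave the study". Neither sentence is limited to one arm.
- **Follow-up of leavers.** Criteria for discontinuing {11b} says: "Subjects who leave the study will be followed up until they are in stable status". It does not say that an M 7 AHI is among what is collected.
- **Analysis set.** Statistical methods {20a} defines the per-protocol (PP) set as "Subjects who complete treatment sessions (M 0 to M 7) without any major violation" and states: "The outcomes will be mainly analyzed using the PP set". The intention-to-treat (ITT) set holds all randomized children.
- **Missing data.** Section {20c} says: "Missing data will be dealt with using the last-observation-carried-forward (LOCF) method".

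The drug arm receives "mometasone furoate aqueous nasal spray once a day (0.1 mg) in the morning for 2 months" (Intervention description {11a}), so its allocated treatment ends 7 − 2 = 5 months before the primary assessment.

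**The concern.** Leaving because of poor response depends on the outcome being measured. The only AHI such a child has before M 7 is the baseline value, so the stated rules offer two treatments of the child, and neither draws on what is known about the response. Tightening the PP definition does not help, because it only moves the child from one treatment to the other.

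What is at stake is the between-arm contrast in the primary endpoint. If two arms lose similar numbers of similar children, the errors roughly cancel. If they do not, the contrast is shifted. Under exclusion, the arm that loses more poor responders is favoured. Under zero change, the direction depends on how those children were really doing.

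**Working it through.** **The plan's own dropout figure.** Sample size {14} expects 80 per group and about 10% dropout. 80 × 1.1 = 88 per group and 4 × 88 = 352, as stated. Ten percent of 88 is 8.8, so about 9 children per arm. This 10% is for all causes and is not split by arm.

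**What LOCF does before M 7.** The last AHI is the M 0 value, so the change is AHI(M 0) − AHI(M 0) = 0, whatever happened to the child.

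**Inputs for the illustration**

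- q, the share of an arm leaving for non-response: 0.10, the whole planned dropout. This is an upper case for that figure.
- m_s, the mean change in stayers: −2.0, the fall cited for medical therapy in Sample size {14}.
- m_l, the mean change leavers would have had at M 7 without the replacement therapy: 0 (unchanged), +2.1 (the rise cited for watchful waiting in the same section), or −0.5 (assumed slight improvement).

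The −2.0 and +2.1 are whole-group means from two different studies. Using them for stayers and leavers is an assumption.

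**Formulas** (positive = the arm's reduction is overstated)

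- True mean: (1 − q)·m_s + q·m_l
- Exclusion reports m_s. Error = q·(m_l − m_s)
- Zero change reports (1 − q)·m_s. Error = q·m_l

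**Results at q = 0.10**

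| Leavers' change | True mean | Exclusion error | Zero-change error |
|---|---|---|---|
| −0.5 | −1.85 | 0.1 × 1.5 = 0.15 | 0.1 × (−0.5) = −0.05 |
| 0 | −1.80 | 0.1 × 2.0 = 0.20 | 0 |
| +2.1 | −1.59 | 0.1 × 4.1 = 0.41 | 0.1 × 2.1 = 0.21 |

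**Effect on a contrast.** If the other arm has no such leavers, these errors pass in full into the contrast. Set against the 2.9 events/h in Sample size {14}, 0.20 is 7%, 0.41 is 14% and 0.21 is 7%. If leavers and stayers behave alike in both arms, the shift is the difference in q times the same bracket. At 5 percentage points it halves: 0.10 to 0.21 under exclusion and 0 to 0.11 under zero change, for leavers at 0 to +2.1.

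**The case against.** **The schedule and exit rule are general, and an article condenses.** Details of early-exit visits and PP membership may sit in the full protocol or analysis plan. That is fair, and the absence of a described leaving visit is not the finding. The main set, the LOCF rule, the assessment times and the exit for poor response are all stated, and the problem is how they combine.

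**Zero may be correct.** If a poor responder's AHI is unchanged, LOCF gives the right value. This stands. With slight improvement, zero even understates that arm's benefit. The direction under LOCF is therefore unknown. Under exclusion, the arm is flattered whenever leavers did worse than stayers.

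**The drug arm is not shown to be the worst case.** A reader might infer that the drug arm is flattered and the benefit of adenotonsillectomy or orthodontics understated, because the course ends at month 2 and the smallest cited fall (2.0, against 3.7 and 15) is for medical therapy. The document does not support this. The exit rule covers all arms, and no exit rate by arm is given. The three falls come from a non-randomized study, and a fall of 15 is hard to reconcile with children enrolled as mild, with an index of 1–5 events per hour. Surgery or a removable appliance could also drive exits; the Discussion names compliance and limited acceptance of randomization as challenges.

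**Larger sizes have no source.** A reader might extend the arithmetic to 20% or 30% leaving (0.82 or 1.23 under exclusion with leavers at +2.1). The only dropout figure in the document is about 10%.

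**The 2-month course.** Comparing with a fixed course assessed off drug is a legitimate choice and is not criticised here.

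**Conclusion.** The concern holds as a weakness in the combined rules, for every arm. A child who leaves before M 7 for poor response is removed from the main analysis for a reason tied to the outcome, or enters with a change fixed at 0.

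At the planned 10% dropout, all of it non-response exit in one arm and none in the other, and with stayers at −2.0, the contrast shifts by 0.20 to 0.41 events/h under exclusion and by 0 to 0.21 under zero change, for leavers from unchanged to +2.1. Smaller differences between arms give proportionally less, and equal losses of similar children give about none. The mechanism follows from the text. The size rests on assumed exit rates and on means borrowed from two studies, and the sign under LOCF is open. Greater exposure of the drug arm is plausible but undocumented.

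**What to change.** 1. **Statistical methods {20a}:** make the ITT set (all randomized) the main set for the AHI ANCOVA, and keep PP as supportive.
2. **Missing data {20c}:** replace LOCF with multiple imputation using arm, baseline AHI, gender, obesity status and reason for leaving. Add a sensitivity analysis that sets the change in non-response leavers over a range from slight improvement (for example −0.5) to +2.1. The range is essential: if few or no leavers have an M 7 AHI, the data say little about how reason for leaving relates to outcome, and imputed values will resemble those of stayers.
3. **Reporting:** give the number, timing and reason for leaving by arm, so that readers can judge whether losses were balanced.

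**Cost.** Somewhat more analysis work, and agreement of the sponsor/researcher and the Ethics Committee under section {25}. ITT may dilute contrasts if many children do not take the allocated treatment; the supportive PP analysis shows how much. The consent form already asks about use of data after withdrawal (section {26b}). No extra polysomnography is required. A sleep study at leaving would add a procedure, and its value would come from before M 7, so it would not be a 7-month result.

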**Fig. 2 Fig2:**
[figure not shown]
The removable twin-block appliance combined with RME used in the orthodontic treatment

Surgery and postoperative orthodontic group: Patients in this group will receive AT under general anesthesia and subsequent orthodontic treatment after surgery. The orthodontic treatment appliance will also be a removable twin-block appliance combined with RME.

### Criteria for discontinuing or modifying allocated interventions {11b}

Participants may quit the study at their guardians’ discretion or defer to the supervisory team. Circumstances that will suspend participants from the study include adverse events and detection of evidence that may influence the outcomes of the research. Subjects who leave the study will be followed up until they are in stable status.

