### Adverse event reporting and harms {22}

Adverse events will be recorded and reported by researchers within 24 h. A supervisory team of three experienced doctors from every research site will be established to assess and manage the adverse events. Serious adverse events will be reported to the Ethics Committee. For subjects in the drug and surgical treatment groups, the observation time for reporting adverse events will be from M 0 to M 7; for subjects who receive orthodontic treatment, the observation time will be from M 0 to the end of orthodontic treatment. Participants may quit the study at their guardians’ discretion or defer to the supervisory team. Circumstances that will suspend participants from study include adverse events and detection of evidence that may influence the outcomes of research. Furthermore, subjects who leave the study will be followed up until they are in stable status.

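### Stopping the allocated treatment is not separated from leaving the study, so a child who leaves before M 7 has no real primary outcome in either analysis set

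*Protocol article*

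**What the plan says.** Section {11b} of the protocol article is headed as dealing with the interventions, but its rules act on study participation: "Circumstances that will suspend participants from the study include adverse events and detection of evidence that may influence the outcomes of the research". Section {22} repeats this almost word for word: "Circumstances that will suspend participants from study include adverse events and detection of evidence that may influence the outcomes of research". Neither section describes a child who is off treatment but still in the study.

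On what happens next, {11b} says: "Subjects who leave the study will be followed up until they are in stable status". Section {30} adds that participants may quit at their guardians' discretion or "defer to the supervisory team if they are not responding well to treatment", and then: "They will be followed up and receive appropriate therapy free of charge after they leave the study". On data, {26b} says that "guardians will be asked if they agree to the use of their children’s data should they choose to withdraw from the trial".

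The analysis sections set the consequences. The ITT set is defined in {20a}: "All subjects will be included in the ITT set after randomization regardless of whether they received the treatment or not". The PP set, also in {20a}, takes children who complete M 0 to M 7 without a major violation, and it carries the main analysis. Missing values are filled by LOCF {20c}. The primary endpoint is the change in AHI from M 0 to M 7, and Table 1 schedules PSG only at M 0, M 7, M 12 and M 24.

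**The concern.** An intention-to-treat comparison needs the M 7 PSG from every randomised child, including those whose treatment was stopped. As written, an adverse event takes the child out of the study, and the follow-up that remains ends at a clinical state rather than at a scheduled measurement. The second ground, evidence that may influence the outcomes, is undefined.

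The four arms are drug, surgery, orthodontic appliance, and surgery followed by appliance. Adverse events and reasons for leaving can plausibly differ between them. If they do, and if children who leave would have fared differently from those who stay, the M 7 comparison is distorted. An analysis plan can choose how to handle missing values, but it cannot recover a PSG that was not done.

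**Working it through.** **1. The plan's own figures (Sample size {14}).** 80 per group × 4 = 320, and 320 × 1.10 = 352, or 88 randomised per arm. A 10% loss leaves 88 × 0.90 = 79.2 per arm. The target effect is given as 0.4 without a scale. It is read here as 0.4 SD, which with the stated difference of 2.9 implies an SD of 2.9 / 0.4 = 7.25 events per hour.

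**2. A child who leaves before M 7.**

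| Step | Source | Result |
|---|---|---|
| PSG values held | Table 1 | M 0 only |
| PP set | {20a} | excluded, M 0 to M 7 not completed |
| ITT set | {20a} | included |
| LOCF value at M 7 | {20c} | the M 0 value, so change = M 0 − M 0 = 0 |
| Consent to use data | {26b} | covers use of the data, supplies no M 7 value |

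The ITT analysis therefore counts the child but uses an imputed zero. A child who leaves after M 7 keeps the primary value, and LOCF carries it to M 12 and M 24.

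**3. Size in a completers-only comparison (illustration).** Assumptions: no true difference between arms; SD 1 in each arm; removed children do d SD worse than retained children; removal shares q1 and q2. Bias = d × (q2 − q1). The standard error is √(1/n1 + 1/n2), with n = 88 × (1 − q), and the test is a two-sided 5% normal test.

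| q1, q2 | d | n1, n2 | Bias (SD) | SE | Type I error |
|---|---|---|---|---|---|
| 10%, 10% | 0.5 | 79.2, 79.2 | 0.5 × 0 = 0 | 0.159 | 0.05 |
| 5%, 15% | 0.5 | 83.6, 74.8 | 0.5 × 0.10 = 0.05 | 0.159 | 0.061 |
| 5%, 25% | 0.5 | 83.6, 66 | 0.5 × 0.20 = 0.10 | 0.165 | 0.093 |
| 5%, 25% | 0.8 | 83.6, 66 | 0.8 × 0.20 = 0.16 | 0.165 | 0.163 |

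Against 0.4 SD, the third row is 0.10 / 0.4 = one quarter of the target. The first two rows average the planned 10% loss. None of the removal shares that differ between arms, and neither value of d, comes from the protocol.

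If d is measured against the whole-arm average instead, the shift in each arm is d × q / (1 − q). For d = 0.5 this gives 0.5 × 0.25/0.75 − 0.5 × 0.05/0.95 = 0.167 − 0.026 = 0.14 SD.

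**4. Size under LOCF in the ITT set.** If leavers make up a share q of an arm and their true mean change is m, replacing it by 0 moves the arm mean by −q × m. The direction depends on the sign of m, which is unknown. This is a different bias from step 3, and the figures there do not measure it.

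**The case against.** Several stronger readings are tempting, and the case against them is good.

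- **A reader might infer that poor response removes a child.** It does not. Section {30} lets such a child leave, and {11b} and {22} do not list poor response among the grounds for suspension. Timing also limits this route: the first scheduled PSG and OSA-20 after baseline fall at M 7, so before then only informal symptom reports could prompt an exit. Poor response bears more on M 12 and M 24 than on the primary endpoint.
- **A reader might infer that PSG stops on leaving.** No sentence says so. The supportable statement is that the protocol does not say assessments continue, and that the follow-up it does promise ends at stable status. Suspension could also mean a temporary pause, but no rule for return is given.
- **A reader might infer a contradiction with the ITT definition.** That definition concerns who belongs to the set, and it is not contradicted. It is weakened, because some members have no post-baseline measurement.
- **A reader might infer that unblinded staff can remove children on the basis of the endpoint.** The text does not say who decides on the second ground or what that person knows. The ground may simply mean that a prohibited co-treatment {11d} was found. The fair criticism is that it is undefined.
- **The 5% against 25% case has no basis in the document.** About 10% dropout is planned {14}, and almost no safety problems are expected {21a}.

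One further objection stands in full. The step 3 figures describe a completers-only comparison, which is close to what a PP-led analysis produces. Collecting the M 7 PSG would not by itself remove that bias while PP remains the main set.

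What survives is the conduct rule itself. It is stated twice, it acts on the study rather than on treatment, and it promises no scheduled assessment afterwards. Deferral to an analysis plan is no answer, because the rule decides who is measured.

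**Conclusion.** The point holds as a defect in the conduct rules. Stopping treatment and leaving the study are not separated, one ground for suspension is undefined, and continued assessment is not stated. A child who leaves before M 7 is absent from the PP set and enters the ITT set with a change of 0, so neither analysis holds real primary outcome data for that child.

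The size cannot be fixed from the document. It ranges from nothing, when removal and prognosis are alike across arms, through 0.05 SD at 5% against 15%, to 0.10 SD at 5% against 25% with removed children 0.5 SD worse. The type I error of about 9% in that last case illustrates assumed inputs and is not a forecast. All of these figures take 0.4 to be in SD units. The change is a cheap improvement; the documents do not show that the trial's result would be overturned without it.

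**What to change.** Amend {11b}, {22} and {30} together so that they agree:

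- A child who stops or changes the allocated treatment for any reason stays in the study and has the scheduled M 7, M 12 and M 24 assessments, unless the guardian withdraws consent to follow-up or an assessment is clinically unsuitable.
- Evidence that may influence the outcomes, such as a prohibited co-treatment, is recorded as a protocol deviation and is not a ground for removal from the study.
- The reason for stopping and any later treatments are recorded.
- The data are used in the all-randomised analysis. Collecting them does not change a PP-led result, so the benefit depends on that analysis being given weight.

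Clinical decisions on stopping treatment are left unchanged, and the sample size stays at 352. The cost is a protocol amendment, some retention effort, and the already planned overnight PSG and imaging in children who have stopped treatment. That is a real burden for those families, but it adds no visit to the schedule.
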